### Objectives

The primary objective is to assess the tolerability of one week of 100 mg oral GPA daily, as compared to placebo. Secondary objectives include the comparison of tolerability with creatine, and the effect of one week of oral GPA on hemodynamic parameters, including peripheral and central blood pressure, and cardiac contractility as compared to creatine and placebo. The tertiary objective is to assess the effect of one week of oral administration of GPA on biochemical parameters, including ADP-induced platelet aggregation [35], compared to creatine and placebo.

### Eligibility

We will include healthy men aged 18 to 50 years, with a normal, nonobese body mass (BMI 18.5 to 29.9 kg/m^2^). Exclusion criteria include high blood pressure or the use of antihypertensive drugs at baseline, (history of) cardiovascular disease including TIA and stroke; the use of plasma CK-increasing drugs including statins; use of acetylsalicylic acid or nonsteroidal anti-inflammatory drugs in the two weeks prior to the first visit; neuromuscular or endocrine disorders; vasculitis; HIV infection; infectious hepatitis; personal or family history of bleeding disorders; sickle cell anemia or other hereditary anemia; smoking; current use or use within two months prior to start of the trial of beta-guanidinopropionic acid or creatine; and abnormalities in glucose, lipid spectrum, thyroid, kidney, or liver biochemistry parameters in the plasma. To stabilize and standardize plasma CK activity during the trial, participants are instructed not to perform exercise three days prior to the baseline visit or during the intervention in the first week [6].

### Statistical analysis

#### Study outcomes

The primary outcome is the tolerability of GPA after oral administration in healthy male volunteers versus placebo as a descriptive measure, in an intent-to-treat analysis. Other outcomes are to compare the tolerability of GPA with creatine, and differences in hemodynamic and biochemical parameters between treatment arms.

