#### Sample size calculation

This is a first-in-man study with GPA, with allometric data available from other species. According to the European Medicines Agency (EMEA) guidelines [36], we will include eight subjects in each arm, to assess the tolerability of GPA versus placebo and creatine over one week.

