### Recruitment strategy

We will utilize two primary resources for identifying and recruiting potential subjects: advertising and identification in our Healthy Volunteer Research Database. The advertisement has prior approval of the MERC. A dedicated trial staff member will respond to inquiries about participation in the trial on the same day, using a participant information letter approved by the MERC. Screening will continue until the target population is achieved (24 subjects). The enrollment period is planned to extend over 9 months, until December 2014.

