**Figure 3 Fig3:**
[figure not shown]
**Trial time line.** Legend: The duration of the intervention is 7 days. The trial supplements start at Day 1, after baseline measurements, inclusion, and randomization at Day 0 (baseline). After 24 h and 7 days of trial supplements, baseline measurements will be repeated, with the last visit at Day 21, to assess side effects.

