### Retention and withdrawal of individual subjects

We will actively monitor retention, and once enrolled, we will make every reasonable effort to follow the participant for the entire study period. In the trial design, we put great effort into limiting the participant’s burden related to visits and procedures, including the calculation of an appropriate NOAEL and HED, and the predominant use of noninvasive assessments. Participants will receive a financial compensation within the MERC guidelines. However, subjects can leave the study at any time for any reason without any consequences. Participants will be given the option to be followed up on certain outcome measures only, if this would lead to retention. Nonadherence will in itself not be a reason to exclude the participant. We will collect the reasons for nonadherence and nonretention where possible. In addition, the investigator can decide to withdraw a subject from the study for any medical reasons. Upon withdrawal, subjects will be replaced.

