## Discussion

Hypertension is still the main risk factor for premature death [1]. Despite the ample availability of antihypertensive drugs and the adequate use whereof, it is estimated that around 10 to 30% of the hypertensive patients are not controlled with currently available drug regimens. Currently, there is an unfulfilled need for new conservative options to treat resistant hypertension [1-5].

This study is based on incremental data indicating that the ATP regenerating enzyme creatine kinase enhances the energy demanding processes involved in hypertension, including vascular contractility and salt retention, and that the creatine analog and competitive CK inhibitor GPA reduces blood pressure in animal studies [5,6,8-16]. Hence, this is a first-in-men study of what might become a new class of antihypertensive drugs. In this study, we will collect data with close adherence to the US FDA and European guidelines. We expect no difference in reported adverse effects between GPA, creatine, and placebo. This study will increase the knowledge on the effect of moderate reversible cytoplasmic creatine kinase inhibition on the human cardiovascular system and provide data on tolerability and hemodynamic parameters. Beta-guanidinopropionic acid doses are low, aimed at preventing toxicity in this first-in-men study. This limits the study of the efficacy of the drug.

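### Intent-to-treat does not fit a tolerability outcome defined after intake: the set can include men who never took a capsule, and it groups men by allocation rather than by product taken

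*Protocol article*

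**What the plan says.** Under Study outcomes, the article defines the primary outcome by what happens once the product has been taken and in the same sentence fixes how it is analysed: "The primary outcome is the tolerability of GPA after oral administration in healthy male volunteers versus placebo as a descriptive measure, in an intent-to-treat analysis". The abstract gives the same rule.

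Four other places bear on who is in that set:

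- **Sample size calculation:** "we will include eight subjects in each arm, to assess the tolerability of GPA versus placebo and creatine over one week". Recruitment strategy gives the total as 24.
- **Figure 3 legend:** randomisation is on Day 0 and supplements start on Day 1.
- **Retention and withdrawal of individual subjects:** a man may leave at any time for any reason, and withdrawn men are replaced. The section does not say whether the man replaced remains in the analysis.
- **Intervention:** intake is observed by trial staff at hospital visits, and pill counts cover doses taken at home.

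**The concern.** Intent-to-treat means every randomised man, in the arm to which he was allocated. Tolerability after intake can be observed only in a man who took something, and it belongs to the product he took. The two definitions part company in two situations that the design allows:

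- a man is randomised on Day 0 and leaves before his first dose;
- a man receives a product other than the one allocated.

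Intent-to-treat protects an efficacy comparison because it preserves the randomised groups. For a tolerability proportion it can put unexposed men in the denominator and credit events to the wrong product. At stake is the only primary outcome of a first-in-man study, a descriptive summary in which one man is one eighth of his arm.

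**Working it through.** **Inputs from the article.** Eight men per arm, three arms: 3 × 8 = 24, which reproduces the stated total. No event rate, dropout rate, alpha, power or margin is given. The number of undosed men and the event counts below are therefore assumptions chosen to show size. The undosed man is assumed to be kept in the denominator without an event.

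**1. GPA proportion with one undosed GPA man, not replaced.** Literal intent-to-treat gives x/8; the dosed men give x/7. The ratio is (x/8)/(x/7) = 7/8 = 0.875, so the figure is 12.5% too low for any x above zero.

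| GPA events x | All randomised (x/8) | Dosed only (x/7) | Gap (points) |
|---|---|---|---|
| 0 | 0% | 0% | 0 |
| 1 | 12.5% | 14.3% | 1.8 |
| 2 | 25.0% | 28.6% | 3.6 |
| 3 | 37.5% | 42.9% | 5.4 |
| 4 | 50.0% | 57.1% | 7.1 |

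**2. The same man replaced but kept in the set.** Nine are randomised and eight dosed. The ratio is (x/9)/(x/8) = 8/9 = 0.889, so the figure is 11.1% too low. With 3 events it reads 33.3% instead of 37.5%.

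**3. Zero events.** The proportion is 0% either way; only the precision it appears to carry changes. The one-sided 95% exact upper limit for 0/n is 1 − 0.05^(1/n): 34.8% at n = 7, 31.2% at n = 8, 28.3% at n = 9. The article plans no such limit, so this is illustration only.

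**4. GPA-placebo difference.** Take 3 GPA events and 1 placebo event. All randomised: 3/8 − 1/8 = 25.0 points. Dosed men only:

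- undosed man in GPA: 3/7 − 1/8 = 30.4 points, so intent-to-treat narrows the difference;
- one undosed man in each arm: 3/7 − 1/7 = 28.6 points, so it narrows it;
- undosed man in placebo: 3/8 − 1/7 = 23.2 points, so it widens it.

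**5. One placebo-allocated man given GPA who has an event.** With no other events, by allocation GPA is 0/8 and placebo 1/8 (12.5%). By product received GPA is 1/9 (11.1%) and placebo 0/7. With 3 other GPA events, GPA moves from 3/8 (37.5%) to 4/9 (44.4%), that is 6.9 points. A shift of 12.5 points in both arms would need two men to exchange products, so that both denominators stay at 8.

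**The case against.** The strongest reply has five parts.

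- **No scoring rule is written.** A reader might infer that an undosed man is counted as having tolerated GPA. The article does not say so. Because the outcome is defined after intake, he could equally be treated as missing. This stands. But leaving him out departs from literal intent-to-treat, so the outcome and the named set still need to be reconciled.
- **No general direction.** A reader might infer a built-in pull towards the result the Discussion anticipates: "We expect no difference in reported adverse effects between GPA, creatine, and placebo". The documents do not support that. Step 4 shows the difference widening when the undosed man is in the placebo arm, and with no GPA events a GPA dropout changes no proportion. This stands in full.
- **Rarity.** Intake is witnessed at visits, Day 1 measurements are timed from intake, the pharmacy supplies products labelled by study number, and withdrawn men are replaced. No dropout or dispensing-error rate is given. This stands and limits the practical weight. Witnessing does not, however, prevent a man from leaving between Day 0 and Day 1.
- **Nonadherence.** The sentence "Nonadherence will in itself not be a reason to exclude the participant" is no evidence of a problem. It keeps men who stop early, possibly because of side effects, and a set requiring at least one dose keeps them too.
- **A condensed article.** A full protocol or analysis plan may define a treated set. That would excuse silence, but here the article names a population for its primary outcome, and the one it names does not match.

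**Conclusion.** The point holds in limited form. The article assigns intent-to-treat to an outcome that exists only in dosed men. Its own timeline and replacement rule allow the randomised and dosed sets to differ, and nothing in it says how replaced men are counted.

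For each never-dosed GPA man kept as event-free, a non-zero GPA proportion is understated by 12.5% in relative terms (8 randomised, 7 dosed), or by 11.1% if he is replaced but kept (9 randomised, 8 dosed). An event in a man given the wrong product would be reported under the wrong arm.

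These sizes rest on one such man occurring and on his being kept in the denominator, neither of which the documents establish. The conclusion is that the stated set should be changed, not that the trial is biased towards finding no difference.

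**What to change.** In Study outcomes and in the abstract, replace the intent-to-treat wording for tolerability with: all randomised volunteers who took at least one dose of trial supplement, grouped by the supplement actually received.

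Add that:

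- randomised but undosed men, and men who were replaced, are listed separately by allocated arm;
- a man who was dosed and later replaced remains in the tolerability set, so that an early withdrawal with side effects is not lost;
- intent-to-treat is kept for the haemodynamic and biochemical comparisons.

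The cost is a few lines of wording and one listing. No new data are needed, because observed intake and pill counts are already collected. The small downside is that the tolerability set may differ from the randomised set by a man or two, which the listing discloses.

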#### Sample size calculation

This is a first-in-man study with GPA, with allometric data available from other species. According to the European Medicines Agency (EMEA) guidelines [36], we will include eight subjects in each arm, to assess the tolerability of GPA versus placebo and creatine over one week.

### Recruitment strategy

We will utilize two primary resources for identifying and recruiting potential subjects: advertising and identification in our Healthy Volunteer Research Database. The advertisement has prior approval of the MERC. A dedicated trial staff member will respond to inquiries about participation in the trial on the same day, using a participant information letter approved by the MERC. Screening will continue until the target population is achieved (24 subjects). The enrollment period is planned to extend over 9 months, until December 2014.

### Clinical investigation

The participants will be instructed to come to the hospital in the morning after an overnight fast for all visits during the intervention, which is the first week of the trial (Visit 1 to 5).

### Intervention

The intervention will be provided under supervision of a medical doctor. The duration of the intervention will be 7 days. To ensure intervention adherence, trial supplements are ingested by the volunteer in the presence of the trial staff during the hospital visits. In addition we will use pill counts for the supplements taken at home.

### Time line clinical studies

The time line is depicted in Figure 3. In brief, clinical studies will be performed at baseline, and 1 day and 7 days after the trial supplements are used. The final assessment of tolerability is at Day 21.

**Figure 3 Fig3:**
[figure not shown]
**Trial time line.** Legend: The duration of the intervention is 7 days. The trial supplements start at Day 1, after baseline measurements, inclusion, and randomization at Day 0 (baseline). After 24 h and 7 days of trial supplements, baseline measurements will be repeated, with the last visit at Day 21, to assess side effects.

### Questionnaire

The participants will receive a questionnaire to assess tolerability at home during the week of intervention and in the 2 weeks after the intervention. The questionnaire encompasses the perceived side effects of the trial supplements, using check boxes and free text space. The questionnaire was piloted with healthcare professionals and healthy volunteers.

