### Study design

We wrote the protocol using the SPIRIT '(Standard Protocol Items: Recommendations for Interventional Trials)' recommendations and the 'Template for Intervention Description and Replication (TIDieR) checklist' [33,34].

The ABC trial is a randomized, placebo and active controlled, double-dummy, participant, intervention provider, and outcome assessor (triple) blinded, parallel group, single center (Academic Hospital of the University of Amsterdam), exploratory trial, with three arms: a primary outcome of tolerability of GPA, in comparison with creatine and placebo.

Randomization will be performed by an independent party, the Clinical Pharmacy Unit of the Academic Hospital of the University of Amsterdam, using a computer-generated, nonadaptive, and restricted randomization scheme and a 1:1:1 allocation ratio. The Pharmacy will generate the random allocation sequence. All participants who give consent for participation and who fulfill the inclusion criteria will be randomized to receive GPA 100 mg and creatine placebo matching active creatine 5 gram; creatine 5 gram and GPA placebo matching GPA 100 mg; or double dummy placebo over 1 week. The participant will receive the blinded, randomized trial supplements from the pharmacy. Allocation concealment will be ensured, as the pharmacy will store the allocation list and not release the randomization code until all outcome measures have been assessed and the data bank has been closed. Thus, randomization will be conducted without any influence of the investigators, outcome assessors, or participant characteristics. After assignment to interventions, trial participants, trial staff, and the outcome assessor will remain blinded to whether the participant was given a placebo or a supplement until after all outcome data have been assessed. Data analysis will be performed unblinded. We prespecified the use of accumulating data to decide whether to stop the trial early, in case of serious or unexpected side effects. Independent monitoring visits will take place before the start of the trial, within 1 month after initiation or after inclusion 5th subject; within 2 months after initiation or after inclusion 15th subject; after last patient last visit; and after the data have been entered into the database. Data entry will be verified by two independent researchers. Budget administration is by an independent organization (AMC Research BV, Amsterdam, the Netherlands).

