### Adverse and serious adverse events

We do not expect any adverse effects from this low dose study. There are no FDA or other reports in formal or informal sources on the side effects of ingestion of this dose of GPA or creatine in animals or humans. Therefore, a 1-day first-in-men study that we had proposed, with hourly observation and physical and laboratory examination of the subjects, was deemed unnecessary by the MERC. Subjects with hypertension, a history of cardiovascular, liver, or kidney disease, or with laboratory abnormalities at baseline will be excluded. Adverse events reported by the included subject spontaneously or through the questionnaire, or observed by the trial staff or health care worker, will be recorded and judged by the study group and the independent physician. The trial staff will convert reported symptoms to a standard lexicon, the Common Terminology Criteria for Adverse Events (CTCAE) [37], to facilitate international scientific reporting. Adverse effects will be classified based on the FDA guideline [29], as overt toxicity (for example, clinical signs, macro- and microscopic lesions); surrogate markers of toxicity (for example, plasma liver enzyme levels); or other adverse effects. The ADR probability scale [38] will be used to assess the causal relationship between trial supplement use and any reported adverse event. Adverse events will be followed until they have abated, or until a stable situation has been reached. Depending on the event, follow-up may require additional tests or medical procedures.

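### The tolerability questionnaire, as described, starts with dosing and asks only for perceived supplement side effects, so prior symptoms cannot be reliably separated from new ones and some symptoms may go unreported

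*Protocol article*

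**What the plan says.** Under Study outcomes, the primary outcome is the tolerability of GPA "versus placebo as a descriptive measure, in an intent-to-treat analysis". Under Sample size calculation, "we will include eight subjects in each arm".

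The Questionnaire section gives the timing: "The participants will receive a questionnaire to assess tolerability at home during the week of intervention and in the 2 weeks after the intervention". It also gives the content: "The questionnaire encompasses the perceived side effects of the trial supplements, using check boxes and free text space". According to the Figure 3 legend, baseline measurements and randomization take place on Day 0 and supplements start on Day 1. The stated questionnaire window therefore begins with dosing.

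Other measures are handled differently. Blood pressure, ECG and hemodynamics have a Day 0 value (Electrocardiography and Hemodynamics), as do the laboratory tests (Laboratory studies). The Abstract takes the biochemical and hemodynamic outcomes as differences from baseline. No Day 0 symptom checklist is described.

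Under Adverse and serious adverse events, events come from spontaneous reports, the questionnaire and staff observation. They "will be recorded and judged by the study group and the independent physician", coded to CTCAE and rated for causality on an ADR probability scale. No section says how a symptom already present before Day 1 is to be recognised.

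**The concern.** There are two separate weaknesses.

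**No pre-dose reference.** A check-box list also picks up complaints unrelated to the supplement. If the volunteer's state before dosing is not recorded, those judging a ticked headache must rely on recall to decide whether it was already there.

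**Attribution before reporting.** The form asks about perceived effects of the supplements, so the volunteer must judge cause before writing anything down. A symptom put down to poor sleep may be left off. The later causality step can discard a wrong attribution, but it cannot recover a symptom that was never reported. The Discussion expects no difference in reported adverse effects between the arms, so under-reporting would push the result towards what is expected.

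At stake is how readable the primary comparison is. With eight per arm and a descriptive reading, a difference of two volunteers is 2/8 = 25 percentage points and will draw comment.

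**Working it through.** **The plan's own figure.** With "restricted randomization scheme and a 1:1:1 allocation ratio" and three arms, 3 × 8 = 24, which matches the recruitment target. The plan states no alpha, power or event rate, so there is no power figure to reproduce.

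**Inputs.** n = 8 per arm is from Sample size calculation. The documents give no symptom rates, so these are assumptions: pre-existing prevalence p of 10–30% and new-onset rate q of 10–20%. Both are taken as independent and equal in the two arms, so there is no treatment effect.

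**Formula.** Let X and Y be the numbers of volunteers with the symptom on GPA and on placebo, independent Binomial(8, r), with f(x) = C(8,x) r^x (1−r)^(8−x). Then P(|X−Y| ≥ 2) = 1 − P(X = Y) − P(|X−Y| = 1), by exact summation.

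**Rates.**
- Every symptom counts: r = 1 − (1−p)(1−q).
- Pre-existing symptoms removed using a Day 0 form: r = q(1−p).

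**Central illustration, p = 20%, q = 10%.**
- All symptoms: r = 1 − 0.80 × 0.90 = 0.28. P(X = Y) = 0.221 and P(|X−Y| = 1) = 0.379, which leaves 0.400.
- Pre-existing removed: r = 0.10 × 0.80 = 0.08. P(X = Y) = 0.403 and P(|X−Y| = 1) = 0.448, which leaves 0.149.

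**Range, chance of a gap of at least 2 of 8.**

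| Pre-existing p | New-onset q | All symptoms count | Pre-existing removed |
|---|---|---|---|
| 10% | 10% | 32.9% | 17.1% |
| 10% | 20% | 40.0% | 31.8% |
| 20% | 10% | 40.0% | 14.9% |
| 20% | 20% | 43.4% | 29.2% |
| 30% | 10% | 43.7% | 12.6% |
| 30% | 20% | 45.1% | 26.3% |

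These gaps are two-sided; the chance that GPA has at least two more than placebo is half of each.

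**Pre-existing symptoms on their own.** With r = p, the chance of a gap of at least 2 of 8 is 8%, 19%, 34%, 41% and 44% at p = 5%, 10%, 20%, 30% and 40%. This is the chance spread of any binary event at that rate with eight per arm. It does not measure what a baseline form would save; the difference between the last two columns of the table does.

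**Reading the columns.** The all-symptoms column assumes that neither the form's wording nor the causality step filters anything. The last column assumes that Day 0 identifies every prior symptom, and it ignores worsening. In this range the chance rises with r, so if judgement and recall remove only some prior symptoms, the value lies between the two columns.

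**The case against.** The strongest reply is that this is a condensed article. It mentions a full study protocol that is not shown, the Figure 3 image is missing, and a Day 0 symptom check may exist. That stands as a caveat: if there is such a check, the sponsor need only state and use it. The objection does not dispose of the point, because the article does fix a questionnaire window and the form's content, and the attribution wording is a problem whatever happens on Day 0.

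Three stronger readings are tempting, and the documents do not support them.
- A reader might infer that prior symptoms are counted as side effects. No section says so. Events pass through judgement and a causality scale, and the form's wording itself invites volunteers to omit old complaints. Misattribution is a risk, not a rule.
- A reader might infer that the GPA–placebo comparison is biased by pre-existing symptoms. Study design describes randomization, placebo, and blinding of participants, staff and outcome assessor. Background symptoms raise the rates in all arms and add noise, but do not shift the contrast on average.
- A reader might treat the 19–44% chance of a gap from pre-existing symptoms (at 10–40% prevalence) as avoidable. Most of it reflects having eight per arm, and a gap of two or more still has a 13–32% chance after the fix.

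Two further objections also stand. The questionnaire is not the only source for tolerability: staff observation, spontaneous reports and laboratory markers contribute. And the two weaknesses partly offset each other, since attribution wording screens out some prior complaints. It does so through the volunteer's opinion, however, and screens out genuine new symptoms as well.

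**Conclusion.** The point holds in a limited form. Followed as written, the main symptom instrument for the primary outcome has no pre-dose reference and filters reports through the volunteer's own view of cause. Treatment-emergent symptoms cannot then be reliably separated from earlier ones, and some may go unreported. The consequence is noise and possible under-reporting in a descriptive comparison of eight per arm.

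Under assumed rates of 20% pre-existing and 10% new-onset, the chance of a spurious gap of at least 2 of 8 falls from about 40% to about 15%. Row by row over the range examined, the reduction runs from about 8 points (40.0% to 31.8%) to about 31 points (43.7% to 12.6%). These are upper estimates of the gain, because they set no filtering at all against perfect removal. The size of any under-reporting cannot be estimated from the documents. The change is worth making because it is cheap; the trial's validity does not hang on it.

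**What to change.** 1. Give the identical checklist at the existing Day 0 visit, before the first dose. If the full protocol already includes a Day 0 symptom check, state it and use it.
2. Reword the form to ask for any symptom, irrespective of presumed cause.
3. Report by arm the symptoms that are new or worse than on Day 0, alongside all reported symptoms.
4. Leave causality to the assessment under Adverse and serious adverse events, made under the blinding set out in Study design.

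The sample size does not change. The cost is one form at a visit already planned, a few minutes of each volunteer's time and slight priming towards symptoms. A single Day 0 snapshot will also miss some intermittent complaints such as headache, so separation will improve but not be complete.
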